### Outcomes measures

#### Primary outcomes

The primary outcomes will be assessed at the end of the study period through quantitative and qualitative data collection. The data will cover participant recruitment and retention, the implementation of the intervention, and participant satisfaction.

The research team will maintain a log book to record: (1) recruitment rate: the number of gynecological cancer patients approached to participate in the study, (2) response rate: the number of patients who met the eligibility criteria and signed informed consent, (3) participation rate: the number of participant attendances in social media-based education and telecoaching sessions, (4) facilitators’ satisfaction rate, (5) participants’ satisfaction rate, and (6) attrition rate: the number of participants who received the intervention and were retained in the study until the final follow-up (week 10).

We will carry out a qualitative evaluation to assess (1) intervention adherence, (2) acceptability of the recruitment processes, intervention design and delivery, and outcome measurements, (3) barriers to recruitment and intervention delivery, and (4) participant satisfaction. Qualitative data will be collected through semi-structured interviews with the participants after the study’s completion. An experienced qualitative researcher will conduct the interviews which will be recorded using an audiotape and transcribed by a research assistant. The qualitative data collection will be terminated when the data reaches saturation.

#### Secondary outcomes

*Sociodemographic and clinical variables*. We will use a questionnaire to collect participants’ sociodemographic data (i.e., age, education, marital status, employment, ethnicity, and religious affiliation). We will also obtain clinical data at baseline from the participant’s medical record, including gynecological cancer type and stage and cancer treatment details.

*Distress*. Distress is defined by the National Comprehensive Cancer Network (NCCN) as a multifactorial unpleasant emotional experience of a psychosocial, and or spiritual nature that may interfere with the ability to cope effectively with cancer, its physical symptoms, and its treatment [25]. The NCCN recommended that distress be recognized, monitored, and managed sufficiently and timely [25]. The NCCN Distress Management Panel also developed the Distress Thermometer (DT), which originated from Roth’s study [26], for the initial, middle, and final distress screening. The DT is a single-item rating scale from 0 (no distress) to 10 (extreme distress) [25]. Participants will be asked to choose the number that best describes the distress level they have experienced over the past week, which could be related or unrelated to cancer. Meta-analyses of studies conducted in Asia and non-English-speaking countries suggested that the optimal cut-off point of DT was four [27, 28]. Therefore, participants who score less than four on the DT are noted to experience mild distress, whereas a distress level of four or above indicates a clinically significant distress level [25]. The DT has been adapted and validated by plenty of studies assessing patients with different cancer types in various languages and countries [25], including Indonesia [29]. The Bahasa Indonesia version of DT, which the NCCN has also verified, will be used in this study to measure the distress level of the participants at baseline and follow-up at weeks 6 and 10.

*Knowledge and practice regarding chemotherapy side effects*. At baseline and follow-up at weeks 6 and 10, the participants will be asked to indicate their knowledge about chemotherapy side effects, how they manage them, and whether they experienced those symptoms in the past week. These outcomes will be measured using the chemotherapy side effect questionnaire outlined by Almohammadi et al. [30]. The questionnaire consists of two subsets. The first part assesses participants’ knowledge of 16 common side effects of chemotherapy, such as nausea and vomiting, fatigue, diarrhea and constipation, mouth ulcers and sores, hair loss, and sexual issues [30]. Yes/no responses will be used in this part of the questionnaire. The second part has seven items to examine the practice of side effect management, for example, "I measure my body temperature" and "I avoid eating spicy or fatty foods." We create four-scale Likert responses (never, seldom, often, and always) in this practice questionnaire. In our prior work, these side effect-related questionnaires have demonstrated their validity and reliability (Cronbach’s alpha of 0.720 and 0.708, respectively).

*Self-efficacy*. Self-efficacy, posited by Bandura as a strong predictor of behavior, is conceptualized as the perceived capability to perform specific actions needed to achieve particular goals [31, 32]. Numerous studies have shown the role of self-efficacy in improving self-management among patients with chronic diseases, including cancer [33, 34].

The self-efficacy for managing chronic disease 6-item scale (SEMCD6) initially developed by the Stanford Patient Education Research Center will be used to measure the participants’ self-efficacy at baseline, week 6, and week 10. This questionnaire is brief and easy to administer as it only contains six items with a Likert scale ranging from 1 (not at all confident) to 10 (totally confident) to indicate how confident a patient is in managing the disease symptoms [35]. The scale’s total score is the mean score over at least four of the six items. A higher score indicates a higher level of self-efficacy. The original version of this SEMCD6 was proven valid and reliable in patients with chronic diseases [35]. Previous studies have shown satisfactory psychometric properties of the several versions of SEMCD6, e.g., Spanish, German, Swedish, and Portuguese [36–38]. This study has assessed the validity and reliability of the Bahasa Indonesia version of SEMCD6. The Cronbach’s alpha value of the SEMCD6 Bahasa Indonesia version is 0.813.

*Sexual quality of life (SQoL-F)*. Sexual quality of life is the primary outcome of our future RCT and will be measured at baseline, week 6, and week 10 using the Sexual Quality of Life-Female (SQOL-F). SQOL-F was initially designed by Symonds, et al. using data sets from women’s health surveys in the United Kingdom and the United States to examine how female sexual dysfunction impacts women’s sexual quality of life [39]. This tool comprises 18 questions that capture sexual self-esteem, emotional well-being, and relationship issues in women. Each item is rated on a six-point Likert scale ("completely agree" to "completely disagree"). Questions 1, 5, 9, 13, and 18 have reversed scoring. Therefore, the total score ranges between 18 and 108. A higher score indicates a higher quality of sexual life [39].

SQOL-F has been translated into some languages, for example, Iranian [40], Portuguese [41], Turkish [42], and Indonesia [43]. In the prior work of this study, the Bahasa Indonesia version of SQOL-F is valid and reliable (Cronbach’s Alpha = 0.751) among Indonesian gynecological cancer survivors.

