## Abstract

Most Indonesian gynecological cancer survivors have unmet supportive care needs during chemotherapy, which may lower their quality of life and discontinue the treatment. Digital health intervention can address this issue. This pilot investigation aims to (1) examine the feasibility and acceptability of a Fighting on distRess, Self-efficacy, Health Effects, and seXual issues (FoRSHE-X) intervention and (2) evaluate prospectively the impact of the study implementation on the level of distress, self-efficacy, side effects’ knowledge and management, and sexual quality of life using the RE-AIM (Reach Effectiveness, Adoption, Implementation, and Maintenance) framework. This is a non-randomized mixed-methods pilot study. We will recruit women diagnosed with gynecological cancer undergoing chemotherapy to participate in the FoRSHE-X intervention consisting of ten weeks of social media-based education and telecoaching. We will evaluate the primary outcomes of study feasibility and acceptability, and the secondary outcomes of study impacts at three time points with quantitative and qualitative inquiries. We anticipate a minimum of 30 participants to enroll in the study and complete the assessment. We will disseminate results through conferences and peer-reviewed scientific journals. This study will imply whether a definitive trial to evaluate the potential benefits of the FoRSHE-X is viable and how it should proceed. The protocol can aid researchers or nurses in implementing this approach in their study or practice.

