### Sampling

We will recruit participants in the DNCC’s One Day Dare Unit and inpatient units. The eligibility criteria will be (1) female aged 18 years or older, (2) being diagnosed with gynecologic cancer (including cervical, ovarian, uterine, vulvar, vaginal, and fallopian tube cancer), (3) receiving chemotherapy at the DNCC, (4) having a smartphone, (5) willing and physically or cognitively able to participate in the study and follow the study procedures, and (6) being able to communicate in Bahasa Indonesia.

On the other hand, patients diagnosed with severe neurological conditions such as unmanaged mental health diagnosis, current metastases to the brain, delirium, and dementia, as well as those with any prior history of receiving chemotherapy or cancer recurrence, will be excluded because these conditions might confound cognitive functioning [24]. Patients with severe hearing or visual impairment that would prevent them from communicating and using the educational digital material will also be excluded. Another exclusion criterion is patients who are single, divorced, or widowed with no sexual partner.

Thirty participants will be recruited using a convenience sampling technique to enroll in the study. A sample size of 30 participants is considered sufficient for evaluating the feasibility of a clinical trial and providing preliminary estimates of the effect sizes of the study outcomes [24]. Before the data collection, the participants will be provided with an explanation of the study activities and their rights, as detailed in the information sheet. The participants will be able to ask questions about any unclear aspects to the researchers and to participate in this research voluntarily. Subsequently, if a participant agrees to be involved in this study, she will sign the Informed Consent Form prepared by the study team. Meanwhile, the participant can withdraw from the study at any time.

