### Data analyses

Descriptive statistics of participants’ clinical and demographic characteristics and all study outcomes will be reported. The recruitment and retention rates will be computed to determine the feasibility of a full RCT. A future complete RCT will be deemed feasible if the recruitment rate is at least 50% and the retention rate is at least 50%. Response rates to questionnaires, follow-up rates, and intervention adherence rates will also be calculated to provide further evidence for the feasibility of a definitive RCT. For the secondary objective, we will compare the longitudinal quantitative outcomes at three-time points (before, at the middle, and after the interventions) using the paired t-test (for continuous variables) and McNemar’s test (for categorical variables), if the data are normally distributed. The non-normally distributed data will be checked using the Wilcoxon test.

Qualitative data will be analyzed using content analysis by the research team’s qualitative researchers. The team will develop a codebook based on the study objective and framework. The predetermined codes include acceptability, implementation, facilitators, barriers, and satisfaction. A qualitative researcher will code the transcripts once the final codes have been defined and agreed upon. Emerging codes can be added to the codebook during the analysis. After the analysis, a detailed description of the findings will be reported. The qualitative findings will inform the acceptability of the study and the strategies or best practices of the study protocol. All research data will be stored in a non-publicly open repository which can be accessed by the principal researcher only to protect participant confidentiality.

The core team for this research consists of nurses with expertise in cancer care. The principal investigator is a professor of nursing who will oversee the study and deliver the telecoaching intervention. The research team members include nurses working in academia and at the DNCC. The nurses at DNCC will help provide a list of patients who may be eligible. In addition, a medical oncology consultant will also be involved in the study implementation process.

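### The pilot's 30 participants are justified by effect-size estimation, but the secondary outcomes, including the future RCT's primary outcome (SQoL-F), are evaluated by significance tests with no interval, change SD or correlation named

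*Protocol article*

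**What the plan says.** Three sections of the protocol article bear on this.

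- **Outcomes measures, Secondary outcomes.** SQoL-F is a secondary outcome here, but its later role is explicit: "Sexual quality of life is the primary outcome of our future RCT". The score is taken at three visits: baseline and weeks 6 and 10. It is an 18-item score, and "the total score ranges between 18 and 108".
- **Sampling.** "Thirty participants will be recruited using a convenience sampling technique to enroll in the study". The size rests on a cited source, and one of its two stated purposes is "providing preliminary estimates of the effect sizes of the study outcomes". The Abstract is slightly different: "We anticipate a minimum of 30 participants to enroll in the study and complete the assessment".
- **Data analyses.** The method given for evaluating impact is this: "we will compare the longitudinal quantitative outcomes at three-time points (before, at the middle, and after the interventions) using the paired t-test". McNemar's test is added for categorical variables and the Wilcoxon test for non-normal data. The same paragraph opens by promising that descriptive statistics of "clinical and demographic characteristics and all study outcomes will be reported". A future RCT is judged feasible if recruitment and retention each reach at least 50%.

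The article gives no significance level, power or target difference for the tests. It does not say how SQoL-F results will feed the RCT's sample size.

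**The concern.** The stated purpose of the sample size is estimation; the stated method for the secondary objective is testing. A test result does not give the size of a change or how precisely it is known, and those are what an estimation aim needs.

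Two things are at stake. First, a verdict on impact taken from tests at this size is unreliable both ways: a modest real change will often miss significance, and one that reaches it will tend to look larger than it is. Second, the RCT will need the SD of SQoL-F and, if it adjusts for baseline, the baseline-to-follow-up correlation. The article does not commit to reporting the change SD, the correlation or any interval. Per-visit means and SDs alone do not determine the first two.

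The point would hold for any paired comparison in this study. It does not depend on the missing control arm or on how the three visits are handled.

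**Working it through.** **The plan's own figure.** The 30 cannot be reproduced. The article gives no alpha, power, effect size, SD, correlation or precision target.

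**Inputs.** From the article: 30 recruited, and a retention criterion of 50%, so 0.5 × 30 = 15 completers would still meet it. Assumed: two-sided 5% level, true standardised changes d (mean change / SD of change) of 0.3 and 0.5, and a correlation of 0.5 or 0.7.

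**Smallest change that can reach significance**, t(0.975, n−1)/√n in change-SD units:
- n = 30: 2.045/√30 = 0.373
- n = 15: 2.145/√15 = 0.554

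The same quantity is the half-width of the 95% CI for mean change. A result at exactly p = 0.05 with n = 30 therefore means d = 0.37 with a CI from 0.00 to 0.75.

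**Power**, noncentral t with noncentrality d√n:

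| True d | n = 30 | n = 15 |
|---|---|---|
| 0.3 | 0.355 | 0.192 |
| 0.5 | 0.754 | 0.438 |

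Power of 80% needs d of about 0.53 at n = 30 and 0.78 at n = 15.

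**Overstatement among significant results** (simulation, true d = 0.3). The mean observed d is 0.51 at n = 30, and 0.51/0.3 = 1.7. At n = 15 it is 0.73 to 0.74, and 0.73/0.3 = 2.4, 0.74/0.3 = 2.5. For the unstandardised mean change the inflation is smaller, about 1.6-fold and 2.1-fold.

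**Why per-visit SDs are not enough alone.** With equal visit SDs, SD of change = visit SD × √(2 − 2r). This is 1.18, 1.00 or 0.77 visit-SDs for r = 0.3, 0.5 or 0.7. For a baseline-adjusted RCT the size factor is 1 − r²: 1 − 0.25 = 0.75 for r = 0.5, and 1 − 0.49 = 0.51 for r = 0.7.

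**What estimation would deliver at this size.**
- SD, chi-square 95% limits as multiples of the estimate: √(29/45.72) = 0.80 to √(29/16.05) = 1.34 at n = 30; 0.73 to 1.58 at n = 15.
- Correlation of 0.5, Fisher z 95% limits: 0.17 to 0.73 at n = 30; −0.02 to 0.81 at n = 15.
- RCT illustration (assumed standardised difference 0.5, two-sided 5%, 80% power, normal approximation): 63 per arm at the point-estimate SD. Across the SD's 95% limits at n = 30 this becomes 40 to 114 per arm.

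**The case against.** The strongest reply has five parts.

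1. **Estimation is planned.** Descriptive statistics of all study outcomes are promised, and preliminary effect sizes are a declared aim. This stands. A reader might infer that the pilot will yield p-values and nothing else; the Data analyses section does not support that.
2. **The planning quantities are obtainable.** A paired t-test uses the SD of change. From a fully reported test, SD of change = mean change × √n / t, and with visit SDs s1 and s2 for the same women, r = (s1² + s2² − SD of change²)/(2·s1·s2). With assumed figures n = 30, mean change 6, both visit SDs 15 and t = 2.19, the SD of change is 6 × √30/2.19 = 15.0 and r = 225/450 = 0.50. This stands too, so it would be wrong to say the study cannot supply them. The route fails for a Wilcoxon test, and the article does not commit to reporting what it needs.
3. **An article may leave such detail to a fuller document.** This is fair for the list of reporting items. It does not cover the mismatch, because the article itself fixes testing as the method for the secondary objective.
4. **The harm is conjectural.** A reader might infer that a non-significant SQoL-F result will be taken as no impact, or will block the RCT. No passage says so. The only numerical go-ahead criteria are recruitment and retention, and feasibility and acceptability are the primary outcomes. The risk is one of interpretation.
5. **The figures depend on what is assumed.** A true change of 0.3 SD is not from the article; at 0.5 SD with 30 completers, power is a respectable 75%. Fifteen completers is the retention floor, while the Abstract anticipates at least 30 completing. Both points stand, so both effect sizes and both sample sizes are shown.

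Even with estimation the correlation would be poorly known. At n = 30 the limits 0.17 to 0.73 put 1 − r² anywhere from 0.97 to 0.47, so the pilot could not distinguish a factor of 0.75 from 0.51. That limits how the correlation can be used; it does not make testing the better choice.

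**Conclusion.** The concern holds as a mismatch between purpose and method. The sample size is defended by estimation and SQoL-F is the intended RCT primary outcome, yet impact is to be evaluated by significance tests plus unspecified descriptives, with no interval, change SD or correlation named.

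At the planned size those tests are a weak basis for a verdict on impact unless the true change is around half a change-SD or more. This rests on a two-sided 5% level and on the assumed effect sizes, neither of which the article states.

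It should be corrected, but it does not threaten the feasibility conclusions.

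**What to change.** In Data analyses, make estimation the main analysis of the secondary outcomes:

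- For each continuous score, give the mean change with a 95% CI, or the Hodges-Lehmann estimate with its CI if the data are skewed.
- For categorical variables, give the paired difference in proportions with its CI.
- State that no conclusion about impact will be drawn from p-values.
- For SQoL-F, also report the SD at each visit, the SD of change and the baseline-to-week-10 correlation, each with a CI.
- State that the RCT sample size will be informed by the SD together with its upper confidence limit, and not by the observed change or its p-value. Use the correlation only with its interval.

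The cost is a change of wording in the analysis plan, with no new data. The report could no longer claim a significant effect, and its estimates would be visibly imprecise.

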### FoRSHE-X intervention

This study intervention consists of two phases of telehealth sessions. Phase I will last five weeks, while phase II will take five weeks. The SPIRIT (Standard Protocols Items: Recommendations for Interventional Trials) 2013 template [44] was used to organize the study’s schedule of enrolment, interventions, and assessment as summarized in Fig 1.

**Fig 1 pone.0299901.g001:**
[figure not shown]
SPIRIT schedule of enrolment, interventions, and assessments.

#### Social media-based education

We developed digital educational media, videos, and infographics, based on clinical guidelines [45] to equip patients with valuable insights and strategies for effectively managing the physical, psychological, and sexual issues that may arise during their treatment journey. The educational contents consist of health management on distress, pain, fatigue, anemia, risk of falling, hair fall, skin problems, sleep problems, difficulty breathing, bleeding, dehydration, constipation, diarrhea, loss of taste and smell, nausea and vomiting, weight loss, edema, sexual issues, and infertility. Our educational materials have been crafted to be visually engaging, featuring eye-catching graphics paired with clear and concise descriptions in Bahasa Indonesia to ensure accessibility and understanding for all patients. Recognizing the prevalence and accessibility of social media, we have chosen to leverage the power of Instagram, one of Indonesia’s most widely used social media platforms, as the vehicle through which we provide this patient education.

#### Telecoaching

Telecoaching, a purposeful and patient-centered intervention carried out by certified nurse coaches using Zoom meetings or WhatsApp video calls, is organized around a ten-step procedure designed to empower and support the participants in applying the knowledge they have obtained from our social media-based education to manage the arising problems related to cancer and chemotherapy. The ten steps are (1) building trust and setting the agenda, (2) finding the inner drive, (3) addressing hidden issues, (4) clarifying orientation, (5) defining goals, (6) identifying options, (7) managing barriers, (8) getting support, (9) taking action, and (10) getting feedback [46].

The first phase lays a solid foundation for the coaching partnership by establishing trust and planning the agenda. The participants’ inner motivation must then be tapped in step two to ignite their desire for proactive self-management. The subsequent step will address concerns that may be hidden and obstruct growth. Step four, clarifying orientation, is crucial in coordinating the patient’s focus with their health objectives. The joint definition of specific objectives and selecting workable solutions to meet those objectives make up steps five and six. In steps seven and eight, the participants will be coached to develop strategies for overcoming obstacles and exploring avenues of external support. Step nine guides patients to take decisive actions after establishing goals and plans. Lastly, receiving feedback in step 10, which brings the coaching process full circle, guarantees that it is dynamic, flexible, and highly responsive to the changing needs and achievements of the individual [46].

